## Abstract

**Background:**

The aim of this study is evaluating the (cost-) effectiveness of a multidisciplinary, evidence based care program to improve the management of depression in nursing home residents of somatic and dementia special care units. The care program is an evidence based standardization of the management of depression, including standardized use of measurement instruments and diagnostical methods, and protocolized psychosocial, psychological and pharmacological treatment.

**Methods/Design:**

In a 19-month longitudinal controlled study using a stepped wedge design, 14 somatic and 14 dementia special care units will implement the care program. All residents who give informed consent on the participating units will be included. Primary outcomes are the frequency of depression on the units and quality of life of residents on the units. The effect of the care program will be estimated using multilevel regression analysis. Secondary outcomes include accuracy of depression-detection in usual care, prevalence of depression-diagnosis in the intervention group, and response to treatment of depressed residents. An economic evaluation from a health care perspective will also be carried out.

**Discussion:**

The care program is expected to be effective in reducing the frequency of depression and in increasing the quality of life of residents. The study will further provide insight in the cost-effectiveness of the care program.

**Trial registration:**

Netherlands Trial Register (NTR): NTR1477

## Background

Depression is a common health problem in nursing home (NH) residents: prevalence rates vary from 6 to even 50% [1-3]. Depression is strongly related to quality of life of NH residents [4], it seriously impacts wellbeing and daily functioning, and increases use of health care services and even mortality [5-7]. The association between depression and quality of life highlights the importance of identifying and treating depression in NH residents with and those without dementia [8,4]. Unfortunately, although depression is a treatable disorder [9], various studies have shown poor detection and undertreatment of depression in NH residents [2,10-12].

Several studies have demonstrated effects of pharmacological and psychosocial interventions for depression in nursing homes [13,14]. The review of Bharucha et al. [15] of 'talk therapies' for depression in long-term care presents evidence for an improvement in depressive symptoms after reminiscence/life review therapy. Moreover, there is evidence for the effectiveness of multifaceted interventions in residential care [16-18] and in nursing homes [19,20].

The Nijmegen University NH Network (UKON), a collaboration between 12 care organizations and the Department of Primary and Community Care of the Radboud University Nijmegen Medical Centre, has developed the care program Act In case of Depression (AID), a multidisciplinary care program to identify and treat depression and monitor treatment effects. The care program is based on and in accordance with the recommendations as formulated in the Supplement Older Adults of the multidisciplinary evidence based guideline for diagnosis and treatment of depression [21] and the Consensus Statement of the American Geriatrics Society and the American Association of Geriatric Psychiatry [22]. The care program is an implementable plan of work that coordinates how the different disciplines should work together, fits in daily practice, and describes how new working methods are related to and can be integrated in the present care process following a step-by-step plan [23].

To date, cost effectiveness studies into the management of depression in NH have not been carried out, but are requested [24]. Gruber-Baldini et al. [10] did find increased involvement of mental health professionals in depressed long-term care residents with dementia, and Smalbrugge et al. [6] found that depressed residents of somatic units had increased use of medication, and received medical specialist consultation and treatment more often than non-depressed residents, implying expensive medical tests and hospital admissions. This paper describes a study that will evaluate the cost effectiveness of the care program AID.

## Methods/Design

The study is a stepped wedge, multicentre intervention study on 14 somatic and 14 Dementia Special Care (DSC) units of UKON-NH.

A stepped wedge design is a type of crossover design in which different clusters (here: units) cross over from the control group to the intervention group at different time points. All clusters are measured at each time point. The first time point corresponds to a baseline measurement where none of the clusters receive the intervention of interest; at the last time point all clusters receive the intervention. After intermediate time points, clusters initiate the intervention. More than one cluster may start the intervention at a time point, but the time a cluster begins the intervention is randomized [25] (see Figure 1 for a graphical representation of the design). This way, comparisons within units ánd between units will be available, making the design very powerful. Another advantage of the design is that all involved units will receive the intervention - which is expected to increase motivation for participating in the study.

**Figure 1 F1:**
[figure not shown]
**Graphical representation of the stepped wedge design**. '0' represents measurement of usual care; control condition '1' represents measurement after the intervention has been implemented; intervention-condition

At the start of the data collection, the residents with informed consent of all 28 units are screened for depression (T0). Following this, each of the units is randomly assigned to one of 5 groups. Each group starts the intervention at different time points, directly after one of the measurements (T0-T4), which are each 4 months apart. In the four- month interval between T0 and T1, nursing staff of the first group is trained within the first month. After this month, the intervention runs for the subsequent 3 months in the first group before the second measurement (T1) of all 28 units takes place. After T1, the second group is trained, and the intervention starts in this group while it is continued in the first group. This procedure is repeated for the remaining 3 groups until, at the last measurement (T5), all 28 units are in the intervention condition. Consequently, the follow up in the intervention condition varies from 3 months for the last group, which starts with the intervention 1 month after T4, to 19 months for the first group, which starts after T0.

### Intervention

Figure 2 shows the care program AID. AID proposes an evidence and practice based standardization of 5 components in the management of depression: 1) identification of depressive symptoms, 2) screening, 3) diagnosis, 4) treatment and 5) monitoring. AID includes standardized use of measurement instruments and diagnostical methods, and protocolized treatment that combines psychosocial, psychological and pharmacological interventions. Cooperation between the disciplines is prearranged. As the ability of nursing staff to detect depression can and should be enhanced [26], the multifaceted and multidisciplinary care program 'AID' starts with a training program for nursing staff on how to identify symptoms of depression using a short observation scale [27] and how to support NH residents with depressive symptoms or depression. Further, AID comprises plans of work for the identification, screening, diagnosing, treatment and monitoring of depression.

**Figure 2 F2:**
[figure not shown]
**Graphical representation of the AID care program**.

#### Identification

nursing staff completes a short observation scale for depression [27] for all participating residents on the unit. If according to the scores on the scale further screening is indicated, nursing staff contacts the psychologist who takes over the coordination on the screening and diagnosing. If no further screening is indicated, nursing staff will complete the observation scale again after 3-4 months.

#### Screening

The psychologist screens the 'identified' residents of somatic units for depressive symptoms with the GDS-8 (Geriatric Depression Scale-NH version; cut-off score 2/3) [28] and those of DSC units with the CSDD (Cornell Scale for Depression in Dementia; cut-off score 7/8) [29-31]. If screening with the GDS-8 in somatic residents is problematic because of cognitive or communication problems, the CSDD will also be administered [32].

For residents with depressive symptoms, i.e. total scores on the GDS-8 or CSDD above the cut-off score, a diagnostic procedure will follow. For other residents, the identification phase will be repeated after 3-4 months.

#### Diagnosing

The elderly care physician and psychologist of each unit perform a diagnostic procedure including the use of chart information, caregiver interview, and examination of the resident (interview, physical examination). Diagnosis of major depression is established according to the DSM-IV-TR criteria. For minor depression the same criteria are used while only 2 to 4 symptoms are present [33,34]. In residents with dementia the Provisional Diagnostic Criteria for depression in Alzheimer's disease are applied (PDC) [35].

#### Treatment

Somatic and dementia residents with depressive symptoms, but without a clinical diagnosis of depression, are offered a personal day structure program made by the nursing staff in collaboration with the recreational therapist. Exercise and music therapy can be part of this day program. Psycho-education is also offered to the resident and/or relatives, including information about depressive symptoms and coping strategies.

Somatic residents with minor depression receive the same treatment as residents with depressive symptoms extended with individual life review therapy. This therapy is based on a protocol that has already been used successfully in Dutch residential care residents and is developed in close collaboration with the Dutch life review expert [name] [36].

Somatic residents with major depressive disorder receive the same treatment as residents with minor depression extended with pharmacological treatment, when deemed appropriate by the elderly care physician. Prescription of pharmacological therapy is in accordance with the recommendations of the Supplement Older Adults [21].

For dementia residents with a PDC-depression diagnosis, treatment includes a personal day structure program, a behavioral management strategy developed by the psychologist and psycho education - especially of relatives. Apart from that, psychological treatment is offered: the clinical experts involved in the development of this care program agreed with recommendations made in the Supplement Older Adults [21] to intervene through the nursing staff (mediative therapy), but stressed that individual contact with the resident is also a necessity. Thus, for dementia residents, psychological treatment comprises of the psychologist supporting and supervising the nursing staff and recreational therapist more intensively in their execution of the day structure program and behavioral management strategy. This support takes place in a regular staff meeting, every two weeks. Within 1 month after the diagnosis, the day structure program and behavioral management strategy should be incorporated in regular care. The psychologist supervises the recreational therapist and nursing staff in at least 2 regular staff meetings. Additionally, if the depression in dementia residents is severe, pharmacological therapy can be given by the elderly care physician, when deemed appropriate.

#### Monitoring

Monitoring with a validated measurement instrument takes place to evaluate treatment. For this purpose, the GDS-8 is used in somatic residents, and the CSDD is used in dementia residents.

### Sampling

We calculated the sample-size using the following assumptions.

For somatic units: 25 residents per unit [37], a depression prevalence of 22% [38], a remission rate of 40% [39], and an attrition of 20% [38].

For DSC units: 20 residents per unit [40], a depression prevalence of 30% [10,40-42], a remission rate of 35% [13], and negligible attrition [40].

Based on these assumptions and a significance level alpha of 0.05, a power of 0.80 and an ICC of 0.1 for both somatic and dementia residents, 14 clusters (units) with 6 measurements are needed in a stepped wedge design to allow multilevel analysis.

Given that the outcomes will be presented on unit-level, during the data collection, newly admitted residents and/or their legal representatives are asked to provide informed consent on all units. This way, the sample size is not influenced by death or relocation of participating residents and can remain stable.

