### Ethical approval

The Medical Ethics Committee of the Radboud University Nijmegen Medical Centre (CMO Arnhem-Nijmegen) rated the study and pronounced that it is not burdensome for the participant. Each NH resident and/or the legal representative on the participating units receives written and verbal information prior to the AID study and is only included in the study after having given written informed consent.

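### Newcomers consent after randomisation, when consent on a crossed-over unit gives immediate entry to AID, so the case mix behind the depression percentage can differ by condition; a sensitivity analysis and neutral consent text would guard against this cheaply

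*Protocol article*

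**What the plan says.** All references are to the protocol article.

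- **T0 residents.** Methods/Design (text under Figure 1) has consenting residents on all 28 units screened at T0, and only then assigns units at random to five step groups. Their consent cannot depend on allocation.
- **Newcomers.** Under Sampling, during data collection, "newly admitted residents and/or their legal representatives are asked to provide informed consent on all units". The reason given is to keep the number of residents stable despite death and relocation.
- **Consent as the entry point.** Under Ethical approval, a resident "is only included in the study after having given written informed consent". Under Intervention, Identification, nursing staff "completes a short observation scale for depression [27] for all participating residents on the unit". Screening, diagnosis and treatment follow from that step.
- **Units still waiting.** Methods/Design says that every unit eventually receives the intervention.
- **Outcome and model.** Measurements defines the first primary outcome as the percentage of a unit's residents with depression. Data-analysis names age, sex, cultural background and cognitive status as covariates. Prior depressive episodes are recorded as an additional measurement but are not a named covariate.

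**The concern.** The request for consent is the same on all units, but what consent offers at that moment is not. On a crossed-over unit, AID is delivered openly by trained staff and a consenting newcomer enters it immediately. On a unit still waiting, the newcomer is measured and meets AID only after the unit's step. Depressed newcomers, or their representatives, may therefore agree more often, or less often, once the unit has crossed over.

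The outcome is a percentage among consenting residents, so it moves with who consents. The shift builds up only in intervention measurements, so unit and period effects do not separate it from the treatment effect. The listed covariates contain no marker of depression history. Keeping the number of residents stable, which is the stated purpose of replenishment, does not keep their case mix stable. At stake is a partly masked benefit or a partly spurious one.

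**Working it through.** **The plan's own figure.** Sampling states "a significance level alpha of 0.05, a power of 0.80 and an ICC of 0.1 for both somatic and dementia residents" and arrives at 14 units per stratum with 6 measurements. I used a Hussey-Hughes variance with two-sided alpha and units split 3/3/3/3/2 (both assumed).

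- Somatic units, 20 residents (25 less 20% attrition): 80.7% power at 14 units and 77.6% at 13.
- Dementia units, 20 residents: 80.6% at 14 units and 77.5% at 13, with a slightly different ICC convention.
- Over all variance conventions tried, power at 14 units is 69-81% (somatic) and 76-85% (dementia).

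The figure of 14 is reproducible and not in dispute. It presumes the same case mix in both conditions.

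**Implied effects (Sampling).** Somatic: 22% × 40% = 8.8 points. Dementia: 30% × 35% = 10.5 points.

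**Step 1: prevalence among included newcomers, with no treatment effect.** The formula is p·c_d / [p·c_d + (1 − p)·c_n], where p is the true prevalence and c_d and c_n are the consent rates of depressed and non-depressed newcomers. The article gives no consent rates. Assumed: c_n = 0.70; c_d = 0.60-0.70 on control units and 0.70-0.80 on intervention units.

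| p | c_d = 0.60 | c_d = 0.70 | c_d = 0.80 |
|---|---|---|---|
| 22% | 0.132/0.678 = 19.5% | 22.0% | 0.176/0.722 = 24.4% |
| 30% | 0.18/0.67 = 26.9% | 30.0% | 0.24/0.73 = 32.9% |

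Difference between conditions:
- 70% against 80%: 2.4 points (p = 22%) and 2.9 points (p = 30%).
- 60% against 70%: 2.5 and 3.1 points.
- 60% against 80%: 4.9 and 6.0 points.
- 70% against 70%: zero.

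**Step 2: share of intervention measurements contributed by post-crossover newcomers.** Only residents admitted after their own unit's step consent under the intervention condition. Five steps and six measurements four months apart give 15 intervention cells (group by measurement): five at 4 months since the step, four at 8, three at 12, two at 16 and one at 20. The mean is (5×4 + 4×8 + 3×12 + 2×16 + 1×20)/15 = 140/15 = 9.3 months. Assume constant turnover such that a share s of residents are newcomers by month 20; the share at t months is then 1 − (1 − s)^(t/20).

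- s = 0.30: 6.9, 13.3, 19.3, 24.8 and 30.0%; weighted mean 15%.
- s = 0.50: 12.9, 24.2, 34.0, 42.6 and 50.0%; weighted mean 27%.

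The weighting treats the five groups as equal in size.

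**Step 3: shift in the unit percentage.** Multiply the share by the difference, taking T0 residents and pre-crossover newcomers to consent at control-condition rates.

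- Lower end: 0.15 × 2.4 = 0.4 points, and 0.36/8.8 = 4%.
- Upper end, somatic: 0.27 × 4.9 = 1.3 points, and 1.32/8.8 = 15%.
- Upper end, dementia: 0.27 × 6.0 = 1.6 points, and 1.62/10.5 = 15%.

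**Opposite direction.** Suppose depressed newcomers consent at 0.8 times the relative rate after crossover, and 20% of those measured are post-crossover newcomers. The shift is then −0.7 points (somatic) and −0.9 points (dementia), about 8-9% of the implied effects, in favour of AID.

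**Turnover as the plan assumes it.** Sampling gives 20% attrition on somatic units, with no period, and negligible attrition on dementia units. If 20% were the loss over the full 20 months, the weighted share would be (5×4.4 + 4×8.5 + 3×12.5 + 2×16.3 + 1×20.0)/15 = 10%. The somatic shift would then be 0.10 × 2.4 to 0.10 × 4.9, or 0.2-0.5 points. On dementia units it would be close to nothing.

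**The case against.** The strongest reply is that the plan asks every unit alike, that every unit gets AID in the end, and that a condensed article need not reproduce its consent procedure. Much of this stands, and it rules out several stronger readings.

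- **That newcomers know their unit's condition.** A reader might infer this from open delivery and trained staff. The article does not say so; it only contains nothing that would prevent it.
- **That consent on a control unit brings only questionnaires.** It also admits the resident to AID after that unit's step. The contrast is between earlier and later access.
- **That the case mix jumps at crossover.** It changes gradually as residents are replaced. Applying the full 30-50% late newcomer share to the differences in step 1 would give 0.7-3.0 points, because it counts people who consented before their unit's step.
- **That the bias masks benefit.** Greater willingness among depressed newcomers would do so; greater reluctance would mimic a benefit. The article does not settle the direction.

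The absence of any statement on who takes consent, or in what words, is no fault in an article of this kind. Sensitivity analyses may likewise sit in a plan that is not shown. What remains is a recruitment rule that the article does fix, post-randomisation consent into an openly delivered programme, justified only by numbers of residents. Neither the uniform request nor the named covariates equalises uptake.

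**Conclusion.** The point holds as a cheap improvement, not as a flaw that undermines the trial. Case mix can differ by condition through newcomers' consent. The plausible size is about 0.4-1.6 points, or 4-15% of the implied effects, and nil if consent is equal. This rests on assumed consent rates (70% in non-depressed newcomers, a 10-20 point difference between conditions in depressed ones) and on assumed constant turnover giving 30-50% newcomers by month 20. With the article's own attrition assumptions it would be smaller, especially on dementia units. The sign is unknown. Residents who consented at T0 are not exposed to this mechanism, which makes them the natural check.

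**What to change.** - Keep the open-cohort, unit-level analysis as primary; it matches the outcome as defined.
- Prespecify a sensitivity analysis of GDS-8, CSDD and EQ-5D restricted to residents who consented before randomisation, and temper the conclusion if its estimates differ materially from the primary ones.
- Report consent rates and newcomers' characteristics at entry, including prior depressive episodes (already recorded), by the unit's condition at the time of consent.
- Use one information and consent text for newcomers that does not name the unit's current condition.

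Two further steps may look attractive but should not be taken. Agreement in size between the two analyses should not be a condition for claiming an effect: that would let a shrinking, less precise cohort veto a design sized at about 80% power. An indicator for inclusion after crossover should not enter the primary model: it is non-zero only under intervention, so it would absorb real differences in effect, for instance from shorter exposure.

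The cost is a few lines of analysis text, one standard information sheet and a consent log by unit and date. The restricted analysis loses precision at late measurements through death and relocation, and it describes a surviving cohort rather than the whole unit.

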### Ethical approval

The Medical Ethics Committee of the Radboud University Nijmegen Medical Centre (CMO Arnhem-Nijmegen) rated the study and pronounced that it is not burdensome for the participant. Each NH resident and/or the legal representative on the participating units receives written and verbal information prior to the AID study and is only included in the study after having given written informed consent.

### Measurements

*Primary outcomes *are frequency of depression and quality of life.

Frequency of depression (the percentage of residents with depression on a unit) is measured in somatic residents by a shortened version of the Geriatric Depression Scale (GDS)[43], the 8-item GDS-nursing home version (GDS-8) of Jongenelis et al. [28], which was made by deleting GDS-items that are not applicable to most NH residents. The GDS-8 was validated in the AGED dataset, where it showed a good internal consistency of α = .80 and high sensitivity rates of 96.3% for major depression and 83.0% for minor depression, with a specificity rate of 71.7% at a cut-off score of 3 or more [28]. The GDS-8 also appears to be able to assess (change in) severity of depression [44]. The GDS-30 is originally a self-report instrument, the GDS-8 is interview based.

Frequency of depression in dementia residents is measured by the Cornell Scale for Depression in Dementia (CSDD)[29]. The CSDD is administered through interviewing nursing staff about their observations of the residents' behavior. The CSDD consists of 19 items each rated as 0 = absent, 1 = mild or intermittent and 2 = severe. The scores of the individual items are summed and a cut-off of 8 or more indicates depression [29]. Vida et al. [30] reported for a cut-off score of 8 or more, a sensitivity of 90% and specificity of 75% in residents with Alzheimer's Disease.

Quality of life in somatic residents is measured by the EQ-5D [45]. The EQ-5D instrument is a standardized non disease-specific instrument for describing and valuing Health Related Quality of Life [46]. There are two core components of the instrument: a description of the respondent's 'own health' using a health state classification system with five domains (mobility, self-care, usual activities, pain/discomfort and anxiety/depression) and a rating of 'own general health' by means of a visual analogue 'thermometer' scale. The EQ5D has shown a good validity and good test-retest reliability [47,48].

In dementia residents quality of life is measured by the EQ-5D proxy version [49]. Thereto, nursing staff are asked to score the scale for the resident.

Secondary outcomes are percentage accuracy of depression-detection in usual care, prevalence of depression-diagnosis in the intervention group, and response to treatment of depressed residents.

*Additional measurements *involve measurement of cognitive functioning by the Mini Mental State Examination (MMSE) [50] and measurement of sociodemographic variables, mental health history - including prior depressive episodes-, present mental health condition - including a dementia diagnosis -, possible treatment for depression, and somatic comorbidity.

Measurements are done by the research team. To study the compliance to the care program, the actual use of all components of the psychosocial, psychological and pharmacological treatment, as well as the factors determining this use, are registered. Accordingly, written checklists are used for nursing staff, recreational therapist, psychologist and elderly care physician, separately.

